### Setting and target population

Individuals with mild or moderate intellectual disability residing in and around Colorado Springs, CO, USA who receive healthcare services from a clinic specializing in developmental disabilities are eligible for the study. Only patients diagnosed with intellectual or developmental disability (IDD) are enrolled at the clinic. The clinic’s medical team determines patient eligibility to enroll at the clinic based on a diagnosis of an intellectual or developmental disability after reviewing available patient records (e.g. medical history, psychological evaluation, school records, developmental disability determination form, etc.). If patient records are limited or unavailable, then clinic staff providers perform medical evaluations to determine eligibility to enroll in the clinic. Eligibility to participate in the study is partially determined by the investigator’s observation of the individual’s functional skills (e.g. communication, ability to follow instructions with assistance, ability to use a computer with assistance, etc.). Ethical permission was obtained through the Institutional Review Board at a major university associated with the study design. All participants provide informed consent before participating. Eligible participants reside in either a group home, host home, family home, or independently. In compliance with ethical guidelines, participants without a legally authorized representative are also included. Individuals with ID who meet the following criteria are eligible for the study: (1) body mass index ≥ 30 kg/m^2^; (2) diagnosis of mild or moderate ID [1]; (3) age 25–50 years; (4) medical provider approval to participate in a weight-loss program; (5) has a regular caregiver willing to participate in a support role unless the participant serves as own legal guardian; and (6) has access to a computer with Internet throughout the week. Exclusion criteria include: (1) already participating in a weight-loss program; (2) a medical condition that prevents safe participation; and (3) insufficient capacity to consent.

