### Intervention

The study design is a 24-week RCT to assess the efficacy of POWERS_*for*ID_ on weight loss and overall health status (target sample: n = 70). The primary aim of this study is to test the feasibility and efficacy of the POWERS_*for*ID_ intervention in obese adults with ID. With a moderate effect size of 0.62 and a two-sided alpha of 0.05, a sample size of 35 participants per group will achieve a power of 0.80. After consent, all participants complete baseline measures and are then randomized to one of two conditions: (1) POWERS_*for*ID_ intervention; or (2) control. De-identified patient demographic data were used to conduct simulation checks to ensure balanced group allocation and to determine a proper randomization protocol. Simulation checks accounted for age, race, and ethnicity. After the simulation checks, a simple randomization sequence was developed. Each individual randomization assignment was then sealed in an envelope. Participants have equal probabilities of randomization to the intervention or control group. When it is time to randomize a participant to either arm, the health coach opens the next envelope in the sequence to reveal the group assignment. Participants are recruited, enrolled, and randomized by the health coach; all other research staff have been blinded to randomization. Participants randomized to the control group receive usual care from the clinic and related clinic staff. In addition, during the 24-week intervention, control group participants complete assessments at baseline, and at weeks 6, 12, and 24. Upon completion of the study period, control group participants are provided educational materials from an online information and resource center specializing in health and disability, as well as the option to contact a toll-free number and speak with an information specialist for further advice on physical activity and nutrition.

Participants randomized to the intervention group receive access to the POWERS_*for*ID_ website and review the interface with the health coach. The participant and coach schedule an initial phone call to review strategies to improve physical activity and diet. Subsequent phone calls occur weekly until the 12th week of the intervention and biweekly during weeks 13–24. All participants visit the clinic at baseline and at weeks 6, 12, and 24. The study protocol is summarized in Fig. 2 (based on SPIRIT 2013 guidelines).

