### Intervention components

#### Health Appraisal Profile (HAP)

The HAP consists of demographics, reporting of primary and secondary disabilities, physical activity level, physical activity barriers, eating behaviors, food frequency, and psychosocial questionnaires [28, 29]. The HAP is administered to both the intervention and control groups at baseline then again at weeks 12 and 24. The HAP is completed by the participant with ID with assistance from the caregiver (if applicable) and health coach.

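### The unblinded health coach recruits, opens the allocation envelopes, coaches one arm and may help both arms with the follow-up self-reports: mainly a risk of bias in the questionnaire outcomes

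*Protocol article*

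**What the plan says.** All references are to the protocol article.

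- **Recruitment and allocation (Intervention).** "Participants are recruited, enrolled, and randomized by the health coach", and everyone else on the research staff is said to be blinded to the allocation. At the moment of randomization, "the health coach opens the next envelope in the sequence to reveal the group assignment". On preparation of the sequence: "After the simulation checks, a simple randomization sequence was developed" and "Each individual randomization assignment was then sealed in an envelope". The same section places consent and baseline measures before randomization.
- **Delivery (Intervention; Goal setting; Nutrition; Coaching calls and motivational interviewing).** The coach reviews the website with intervention participants, agrees goals and targeted foods with them, and holds weekly calls to week 12 and biweekly calls in weeks 13–24.
- **Self-report outcomes (Health Appraisal Profile).** The HAP is given to both arms at baseline and weeks 12 and 24, and is "completed by the participant with ID with assistance from the caregiver (if applicable) and health coach". The Outcomes section words the help as optional, from a caregiver, the coach or both. The HAP questionnaires section lists activity, barrier, self-efficacy, fruit-and-vegetable, depression, psychosocial and food-frequency instruments.
- **Other outcomes (Outcomes, Table 2).** Weight is measured in the clinic, clinicians measure waist and body composition, and lipids come from blood tests taken from medical records.
- **Analysis (Data analysis).** A project coordinator and a statistician, both described as blinded, fit mixed models to each outcome and look for a group-by-time interaction.

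**The concern.** One role combines four tasks that are better kept apart: choosing whom to approach, revealing the assignment, delivering the treatment and helping to record outcomes. Because every other member of the research staff is said to be blinded, the coach is the one research role stated to know the arm.

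The self-report outcomes are the most exposed. By week 12 the coach has spoken weekly with each intervention participant about diet and activity. The same coach may then help that participant, an adult with intellectual disability, answer questions about those behaviours. Control participants have no such relationship with the coach. Prompting and a wish to please can therefore differ between arms without any misconduct, and the difference would be read as a treatment effect.

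The second exposure is at entry. If the recruiter learned an assignment before completing an enrolment, the arms could differ in motivation or ability from the start. Concealment depends on the same person who will coach one of the arms.

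**Working it through.** The plan gives no figure for this point. Its effect size of 0.62 and power of 0.80 are not tied to any questionnaire, so they are not used as a yardstick here.

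**1. Does coach help reach the estimated effect?** Write the expected follow-up score in each arm as the true mean plus a shift from assistance, b_I (intervention) and b_C (control). The baseline HAP is completed before randomization, so assistance then cannot depend on the arm. The expected difference between arms in change from baseline is

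true effect + (b_I − b_C).

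Equal shifts cancel and unequal ones do not. The remainder falls in the group-by-time term that the Data analysis section tests. Blinding the analyst does not alter it, because it is already in the recorded answers.

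**2. How much could it matter?** This is an illustration only. The assumptions are a single two-sided 5% comparison of one follow-up score, no true effect, and a differential shift of b SD. The planned mixed model would give somewhat different values. With n per arm and s = b / √(2/n), the false-positive rate is

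1 − Φ(1.96 − s) + Φ(−1.96 − s).

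For n = 35 (Intervention section), √(2/35) = 0.239. With b = 0.2, s = 0.837 and the rate is 0.131 + 0.003 = 0.133 (unrounded terms). With the hypothesised 70% retention (Data analysis), n = 0.70 × 35 = 24.5.

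| Assumed differential shift (SD) | 35 per arm | 24.5 per arm |
|---|---|---|
| 0 | 5% | 5% |
| 0.1 | 7% | 6% |
| 0.2 | 13% | 11% |
| 0.3 | 24% | 18% |
| 0.5 | 55% | 42% |

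**3. Can the coach predict the next assignment?** Not from the sequence. It is simple, and "Participants have equal probabilities of randomization to the intervention or control group", so each assignment has probability one half whatever came before. Foreknowledge would require defeating the seal or opening an envelope before enrolment is complete. The article describes no one other than the coach at that step, so protection rests on the envelope and on the coach's conduct.

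**4. Which outcomes are exposed?** Coach help is described only for the HAP. Weight, waist, body composition and lipids are obtained by the clinic, so this mechanism does not reach their recording.

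**5. Is the stated blinding a full safeguard?** The project coordinator is called blinded, yet arranges the first coaching call (Goal setting) and reviews call logs and 20% of call checklists (Fidelity). Coaching calls are described only for the intervention arm. The coordinator is therefore not a suitable replacement as HAP assistant.

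**The case against.** The strongest reply concerns allocation. A reader might infer that assignments are open to the recruiter and that nothing separates knowing the next one from deciding to enrol. The article does not support that: assignments are sealed, the sequence is unpredictable, and consent and baseline come first. Who keeps the envelopes is not stated. Opacity, numbering and custody are details that an article may leave to the full protocol, so their absence is not held against the plan. This part of the reply stands, and it reduces selection bias to a secondary risk.

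A reader might also infer that the coach makes the subjective eligibility judgement. The Setting and target population section begins "Eligibility to participate in the study is partially determined by", but goes on to name the investigator's observation of functional skills. It does not name the coach, and it also requires a diagnosis and a medical provider's approval. This too stands.

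Third, coach help with the HAP is optional under the Outcomes section, and the main body measurements are taken by the clinic. That confines the assessment problem to self-reports but does not remove it. The HAP section states the coach's assistance without qualification, and neither section restricts it at follow-up or by arm.

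Finally, caregivers are no blinded alternative. They have a support role, may join calls and can view progress on the system. This limits what any fix can achieve.

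**Conclusion.** The point holds for the self-report outcomes. The stated roles allow the only research role known to be unblinded, which is also the one delivering treatment, to help record those outcomes in both arms after randomization. Any difference in prompting or in the wish to please passes straight into the group-by-time effect.

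Selection bias remains a lesser exposure. Nothing shows that it occurred, and the partial safeguards are real. The weakness is that concealment relies on a recruiter who is also the coach.

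A reader might go further and conclude that the trial as a whole is biased, weight result included. The documents do not support this, because weight, waist, body composition and lipids are measured in the clinic.

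The size is unknown. The rates of 13% to 24% rest on an assumed differential shift of 0.2 to 0.3 SD, 35 per arm and one unadjusted comparison. Some sections refer to coaches in the plural, but the conflict of roles is the same with one coach or several. The change is worth making, though the point does not invalidate the design.

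**What to change.** (a) **Allocation, for participants still to be enrolled.** Log the participant ID, eligibility and completed baseline first. Then have the assignment released by an existing person who neither recruits, coaches nor analyses the data. Baseline before randomization is already the plan; the changes are the log and the separate release.

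(b) **Follow-up HAP, weeks 12 and 24.** Any staff help should come from existing clinic or research staff who do not know the arm and have no part in coaching logistics, and not from the coach. Table 2 also lists several of these instruments at week 6; the same rule should apply wherever they are given after randomization. Where a caregiver assists, acknowledge that the caregiver is unblinded. Record who assisted at each visit in both arms, and report the self-report results as open to this bias.

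**Cost.** Some scheduling effort at clinic visits that already take place. The HAP contains about ten instruments, so the time needed is not trivial. Treatment, sample size and endpoints are unchanged. Recruitment began on 20 September 2016 and is described as open, so (a) cannot help participants already randomized, while (b) can still help those with follow-up visits to come.

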**Fig. 2 Fig2:**
[figure not shown]
SPIRIT 2013 diagram for study protocol and outcomes

### Intervention components

#### Health Appraisal Profile (HAP)

The HAP consists of demographics, reporting of primary and secondary disabilities, physical activity level, physical activity barriers, eating behaviors, food frequency, and psychosocial questionnaires [28, 29]. The HAP is administered to both the intervention and control groups at baseline then again at weeks 12 and 24. The HAP is completed by the participant with ID with assistance from the caregiver (if applicable) and health coach.

#### Goal setting

After the participant and caregiver (if applicable) complete the baseline HAP, the individualized (automated) goals and objectives are generated by the POWERS_*for*ID_ system and reviewed by the health coach before the first online meeting and phone call with the participant. After the health coach and the participant agree to the physical activity, nutrition and behavioral reinforcement plan, the project coordinator arranges the first coaching call. The initial call lasts approximately 30–60 min and is used to review the goals and implementation strategies selected by the POWERS_*for*ID_ system (established from the baseline HAP) and to set a schedule for the weekly (first 12 weeks) and biweekly (last 12 weeks) coaching calls, which last approximately 20–30 min. The goals and implementation strategies in physical activity and nutrition are finalized with the participant to ensure that they are consistent with the participant’s abilities, interests, and availability of community resources. Discussion points are noted by the health coach, permitting the research staff to review calls and monitor recommendations. During the calls, participants learn new strategies to improve their nutrition and physical activity behaviors (e.g. viewing a video of a certain activity, learning about healthy food choices) and are able to check the website with a password protected ID at any time for updates on their progress. Caregivers also have access to the system to view the progress of their care recipient.

#### Physical activity

Physical activity goals are set at a minimum of 30 min of aerobic exercise per day for the first four weeks of the intervention and gradually increased to 60 min per day (can be done in one or more sessions per day) during weeks 5–24, as reviewed and recommended by the person’s physician. The 60-min recommendation is based on the American College of Sports Medicine’s physical activity guidelines [30]. The participant also has the option to document strength and flexibility exercises. Participants receive physical activity options based on their interest level, what is available in their community, and affordability. The health coach may also provide recommendations and assist the participant with problem-solving perceived barriers to physical activity. Additional resources and recommendations are auto-populated by POWERS_*for*ID_. Each participant is given a pedometer to cross-validate their self-reported physical activity level.

#### Nutrition

The participant and coach select the nutrition goals. During the initial phone call, the participant and coach review food suggestions populated to POWERS_*for*ID_ from the HAP food frequency questionnaire. The participant and coach collectively identify and discuss “problem” foods (i.e. foods high in fat, carbohydrate, and caloric value) and agree on strategies to reduce consumption of one or more of these foods. The participant is also given instructions on what constitutes a serving size for each food group, as well as proper methods for measuring foods. After agreeing on targeted foods, the health coach populates the food item(s) into POWERS_*for*ID_ along with their corresponding nutritional values. The participants then log their daily consumption of these target foods with assistance from their health coach.

#### Reinforcement system

The reinforcement elements located on the POWERS_*for*ID_ profile page include a set of symbols associated with completion and logging of a day’s physical activity and nutrition goals. Small incentives are mailed or given to participants when they meet their target “healthy” points for the week ($2 for attaining 100% of weekly goals and prorated accordingly for achieving a lower percentage or $1 if 50% of goals are achieved). Participants who are adherent to the protocol (based on their physical activity and nutrition scores) receive a phone call from the health coach to compliment them on having a successful week.

#### Coaching calls and motivational interviewing

Coaching calls are used to support participants and last approximately 20–30 min. The calls provide an opportunity to review participant progress, discuss barriers or setbacks, and identify future objectives. The calls occur weekly during the first 12 weeks of the intervention and biweekly in weeks 13–24. Each phone call is scheduled with the coach, participant and caregiver (if applicable) in advance. Prior to a phone call, the coach reviews any notes or discussion board posts as well as notes from previous phone calls and information logged by the participant on the POWERS_*for*ID_ website.

During the phone call, coaches utilize MI techniques adapted for individuals with ID [23]. MI has been demonstrated as efficacious for changing health behaviors [31]. MI typically involves abstract reasoning, but adaptations respectful of an individual’s cognitive level may still render motivational interviewing effective [23]. In addition, MI allows for person-centered interactions. The health coach provides guidance and suggestions but does not make decisions; it is up to the participant to decide on his/her best course of action. The coach’s use of MI techniques and participant response are analyzed via qualitative methods described below.

#### Additional materials

In addition to having access to the POWERS_*for*ID_ website and coaching calls, participants in the intervention group also receive additional materials to aid in study progress and behavior monitoring. These materials include a pedometer to monitor step count, flyers with information on logging into the website, a bathroom scale (only if the participant does not own an appropriate scale) with a guide to weighing themselves frequently, and nutrition handouts. Scales are to be returned once the participant has completed the entire study. These additional materials support the participant between coaching sessions as well as promote objective reporting.

### Outcomes

Outcome measures and timing of administration are listed in Table 2. Clinic visits include routine care, the HAP, and measurement of body weight and body composition (via waist circumference and bioelectrical impedance analysis). Blood samples for measurement of lipids and blood sugar are collected at baseline and week 24. Participants will be required to visit their medical provider at baseline and weeks 6, 12, and 24. During the visits, participants will receive medical supervision that mimics the routine care provided by the clinic. Routine care consists of measuring a patient’s blood pressure, 0_2_ saturation, urinalysis, height, weight, and waist circumference. Medical records will be accessed to collect the participant’s blood sample results. For the POWERS_*for*ID_ intervention clinicians will also measure body composition via bioelectrical impedance analysis and waist circumference. Standard procedures for assessing anthropometrics, such as removal of additional clothing items, measuring from between the lowest rib and iliac crest for waist circumference, will be utilized in line with standardized clinical procedures. The HAP is completed following completion of clinical measures and may be completed with assistance from a caregiver (if applicable) and/or the health coach.

**Table 2 Tab2:** Outcome measures, instruments, and time points

Measures	Instruments	Time point(s)
Adherence	Logs, enrollment metrics, tracking data	Daily
Demographics	Demographics	Baseline
Functional abilities	POWERS_*for*ID_ disability, health and function	Baseline
Body weight	Scale and bioelectrical impedance analysis of body composition	Clinically measured at baseline and weeks 6, 12, and 24
Physical activity behaviors	Physical Activity and Disability Scale; Barriers to Physical Activity and Disability Scale; Exercise Perception Scale; Self-Efficacy Related to Exercise for People with DD Scale	Baseline and weeks 6, 12, and 24
Physical activity	Physical activity points and steps (pedometer)	Daily
Barriers to PA	Barriers to Physical Activity and Disability Scale	Baseline, weekly, 24 weeks
Nutritional behaviors	Block Food Frequency Questionnaire; Fruit and Vegetable Self-Efficacy Scale; Fruits and Vegetables Outcomes Expectancy Scale; Barriers to Fruits and Vegetables Scale	Baseline and weeks 6, 12, and 24
Nutrition	Healthy eating points	Daily
Dietary barriers	POWERS_*for*ID_ dietary barriers	Baseline and weeks 6, 12, and 24
Psychosocial	*HealthMatters* psychosocial questionnaire; Glasgow Depression Scale for people with a Learning Disability	Baseline and weeks 6, 12, and 24
Evaluation of POWERS_*for*ID_	Semi-structured interviews (qualitative analysis)	Post-intervention
Lipids	Blood test	Baseline and 24 weeks

#### HAP questionnaires

Questionnaires used in the HAP have been specifically designed for and previously utilized in populations with intellectual and developmental disabilities except for the Block Food Frequency Questionnaire. Questionnaires include: Physical Activity and Disability Scale [32], Barriers to Physical Activity and Disability Scale [33], Exercise Perception Scale [34], Self-Efficacy Related to Exercise for People with DD Scale [35], Fruit and Vegetables Outcome Expectations Scale [36], Fruit and Vegetable Self-Efficacy Scale [37], Barriers to Eating Fruits and Vegetables Scale [38], Glasgow Depression Scale for people with a Learning Disability [39], psychosocial questionnaires reproduced from the *Health Matters* curriculum – a health behavior curriculum for individuals with intellectual and developmental disability [28], and the Block Food Frequency questionnaire.

Semi-structured interviews are also obtained post intervention to gather qualitative data from intervention participants and caregivers. Three questions are used: (1) What barriers and facilitators were associated with implementing the recommendations? (2) What strategies were and were not effective in changing behavior? and (3) What additions would you recommend for the POWERS_*for*ID_ intervention?

